Inclusion and exclusion criteria for participants with PAD are displayed in Table 1. In addition, criteria for discontinuing allocated interventions are presented in File S1 (Item 11b). Participants provide paper-based written, informed consent before they participate in the study (File S2), which is collected by the assessor at visit #1 (inclusion visit, Figure 1). At visit #1, the order of the treadmill test and 6 min test is first randomized electronically, and the information is given to the assessor of the local center where the participant performs both tests accordingly. Once visit #1 is achieved, following an electronic process (File S1, Item 16a), each participant is randomized into one of the two arms (1:1) of the study: (1) NMES group; or (2) Control group (CONT). Randomization is performed as block randomization with a 1:1 allocation. The randomization is stratified and equilibrated (block for equilibration not provided here to preserve concealment allocation) in the five inclusion centers. Only the biostatistician, the data manager, and the research associate at the coordinating center have access to the allocation sequence to preserve the allocation concealment. In that way, the assessor of the different outcomes in each center is blinded to the participant treatment group allocation. The research associate of the coordinating center receives an email mentioning the participant group allocation. Then the research associate mails a box containing the following to the participant’s home:for both groups of participants: (i) a box containing the monitors for daily physical activity (PA) and outdoor walking-capacity assessment; (ii) a handbook that explains how to wear the monitors, how to perform the outdoor walking sessions, and that includes a diary to report different information (see below and File S3); (iii) a sealed envelope containing a brochure with advice for regular PA on a day-to-day basis (File S4).for the NMES group only: (i) an opaque box containing the NMES device; (ii) a sealed envelope containing the NMES handbook for implementation and follow-up of the NMES program (Files S5 and S6).

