To enhance validity of data, for each NMES session, participants are asked to report the following information in a diary: stimulated calf(s), NMES intensity level maintained during the session, cumulated total duration reached at the end of the session, and feelings about the session. To assess protocol adherence, the ratio of the total duration of NMES reached at the end of the protocol over the expected total duration will be used in future analyses. In addition, phone calls are also conducted every two weeks (±4 days) to record information about the NMES program to ensure the correct functioning of the device, check the correct number of hours of NMES performed, promote participant retention, and complete follow-up. The participants are also asked to indicate whether any changes in symptoms, comorbidities or walking activity potentially occurred. Furthermore, participants in the NMES group receive a brochure with advice for engaging in daily PA (File S4).

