### 2.7. Sample Size

The calculation of the number of participants per group was based on the expected improvement in the MWD after 12 weeks in the intervention group (NMES) compared with the control group. Considering previous studies [12,14] that assessed the effects of NMES during a program of lower duration (1 month), we expected a 50% improvement in MWD in the NMES group with no significant change in the CONT group. We assumed a baseline MWD of ~115 ± 78 m in both groups. Thus, considering a between-groups difference of approximately 58 m with a standard deviation of 78 m at the end of the 12-week program, the minimum number of participants to be included in each group is approximately 29, with an alpha risk of 0.05 and a power of 80%. We anticipated that the total number of participants to be included could be 80 (40 per group), allowing for a maximum ~30% dropout rate.

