### 2.8. Data Collection, Management, and Analysis

*Data collection and management.* The data collected are in an electronic Case Report Form (eCRF) and data monitoring is carried out on a regular basis (~every six months).

*Statistical analysis (see also File S1, item 20a).* Descriptive statistics will be performed to describe the baseline characteristics of interest at the level of the two groups and for the different outcomes. Continuous data will be expressed as mean +/− standard deviation or median values with interquartile range, depending on the distribution. A normality test will be carried out to judge the Gaussian or non-Gaussian distribution of the data of the continuous variables studied. Two-sample, two-sided t-tests (or Mann–Whitney U test) and χ2 tests will be used to compare continuous and categorical characteristics of participants across the two groups at baseline, respectively.

For statistical analysis of the primary and secondary outcomes after study completion, two -sample, two-sided t-tests (or Mann–Whitney U test if the data is not normally distributed) will be used to compare changes in outcomes between baseline and the 3-month follow-up between the NMES and the CONT groups. However, in case of imbalance in baseline characteristics between the 2 groups, outcome data will be analyzed using linear regression models adjusting for significantly different baseline data between the two groups [46].

Firstly, an intention-to-treat analysis will be performed. As recommended [47], a missing at random (MAR) assumption will be made for missing data for principal analysis by performing complete cases and multiple imputation analysis. Deviation from MAR will also be assessed with sensitivity analysis under the missing not at random (MNAR) assumption, using controlled multiple imputation with different controlled scenarios. A per-protocol analysis will be also performed considering only participants with data available both at visit #1 and visit #2.

A subgroup analysis will be performed to explore the potential association between change in treadmill MWD and reported walking activity changes during the follow-up. In the NMES group, potential association between the total dose of NMES over the program and change in treadmill MWD will be assessed.

Statistical analysis will be carried out using R software [48]. The level of significance will be fixed at *p* < 0.05.

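### For the primary outcome the per-protocol set is the complete-case set, with no adherence criterion, and complete cases and multiple imputation share the principal role without an order

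*Protocol article*

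**What the plan says.** Section 2.8 puts an intention-to-treat analysis first. Missing data are handled under a missing-at-random assumption "for principal analysis by performing complete cases and multiple imputation analysis", followed by controlled imputation under missing-not-at-random scenarios. It then adds: "A per-protocol analysis will be also performed considering only participants with data available both at visit #1 and visit #2".

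Section 2.5 defines the primary outcome as the 12-week change in treadmill MWD. Section 2.8 fixes the test: "two-sided t-tests (or Mann–Whitney U test if the data is not normally distributed) will be used to compare changes in outcomes".

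Section 2.3 says adherence will be measured by "the ratio of the total duration of NMES reached at the end of the protocol over the expected total duration", drawing on session diaries, and that this ratio will be used in future analyses. The per-protocol definition does not refer to it. Section 2.8 also plans to relate total NMES dose to MWD change, within the NMES group only.

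**The concern.** A per-protocol analysis is normally read as a check on what happens when the intervention is delivered as planned. That question is natural here: the programme is unsupervised, runs at home for 12 weeks, and the participant sets the intensity. The stated definition selects on attendance at the follow-up visit and not on treatment received. A report following it would show a complete-case result and a per-protocol result that match because they are the same analysis, and a reader could take the match as robustness to non-adherence.

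The second issue is the decision rule. If complete cases and MI are both principal and one is significant while the other is not, the text does not say which is the trial's answer.

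**Working it through.** **1. Comparing the sets for the primary outcome.**
- Complete case: MWD change is observed, which requires MWD at visit #1 and at visit #2.
- Per-protocol as stated: data at visit #1 and at visit #2.
- Difference between the sets: 0 participants. The data and the test are also the same, so the results are the same.

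This is shown for the primary outcome only. Secondary outcomes can be missing in people who attended both visits.

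**2. What the rule admits and excludes.** From the schedule in Section 2.3, expected NMES time is 5 days × (8 weeks × 2 h + 4 weeks × 3 h) = 5 × 28 = 140 h. A participant with 0 of 140 h who attends visit #2 is in the set. One with 140 of 140 h who misses visit #2 is out.

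**3. The plan's own sample size, to anchor the simulation.** Inputs from Section 2.7: "a between-groups difference of approximately 58 m with a standard deviation of 78 m at the end of the 12-week program", two-sided alpha 0.05, power 80%. Then n per group = 2 × (1.96 + 0.84)² × 78² / 58² ≈ 28.4, rounded up to 29. This matches the article: "the minimum number of participants to be included in each group is approximately 29". The t-based solution is 29.4. The point raised here does not dispute this figure.

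Section 2.7 recruits 40 per group and allows for dropout of at most about 30%. At that limit 40 × 0.70 = 28 per group remain, so 12 per arm are missing and both sets hold 56 of 80 participants.

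**4. Effect of two unranked principal analyses.** Simulation with 40 per arm, 12 per arm missing at random and SD 78 m; 4000 trials per scenario. A complete-case t-test on change is compared with MI. The baseline/follow-up correlation is not in the document and is assumed.

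| Assumed correlation | Different verdicts at 58 m | Either significant, no effect |
|---|---|---|
| 0.5 | 8.1% | 6.1% |
| 0.7 | 2.6% | 5.7% |

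The Monte Carlo standard error of the last column is about √(0.06 × 0.94 / 4000) = 0.4 percentage points.

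**5. Sensitivity to the assumptions.**
- With 6 missing per arm (15%), different verdicts at 58 m fall to 4.1% (correlation 0.5) and 0.9% (0.7).
- Suppose instead that average dropout is near 28% but depends strongly on baseline MWD, in opposite directions in the two arms (correlation 0.5 to 0.8, no true effect). The complete-case test then rejects in 8.8% to 16.1% of trials, MI in 4.4% to 4.7%, and either of the two in 10.4% to 18.1%. This dropout pattern is an assumption. The document gives no evidence for it.

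**The case against.** The strongest reply is that this is a superiority trial with intention-to-treat stated first. A supportive set with a poor label cannot overturn the primary conclusion. That stands, and it limits the severity.

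The article also cites File S1, item 20a, which is not shown and may rank the two methods or add criteria. Ranking methods and setting an adherence cut-off are commonly left to the analysis plan. However, the article does not leave the per-protocol set open: it states a definition, and that definition does not do what its name says. If File S1 differs, the two need to be reconciled.

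Three stronger readings are tempting, and the document does not support them:
- A reader might infer that intention-to-treat and per-protocol must agree by construction. The identity holds only against the complete-case half. MI and the missing-not-at-random analyses can differ from it.
- A reader might infer that adherence is ignored altogether. It is not: the NMES-group dose analysis is planned and the adherence ratio is collected. That analysis is not a between-group comparison, though, so it does not replace a per-protocol analysis.
- A reader might infer serious type I error inflation. With data missing at random in both arms it is about one percentage point, and that is at a dropout level which Section 2.7 gives as a maximum and not as an expectation.

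Redefining the set by adherence has its own weakness. The ratio exists only in the NMES arm, so selecting adherers breaks randomisation.

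**Conclusion.** The point holds, at moderate severity. For the primary outcome, the per-protocol analysis duplicates the complete-case analysis exactly and carries no information about non-adherence. This follows from the definitions and needs no assumption.

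Separately, Section 2.8 does not fix which of complete cases and MI is decisive. At the stated maximum dropout, with data missing at random and a correlation of 0.5 to 0.7, the two disagree in about 3% to 8% of trials at 58 m, and counting either as success gives a type I error of about 6%. Both figures shrink with less dropout. They could be larger if dropout differs by arm and relates to baseline MWD.

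**What to change.** 1. Name one principal analysis: MI on all randomised participants, with arm, baseline MWD and centre in the imputation model. Make complete cases a sensitivity analysis beside the planned missing-not-at-random scenarios.
2. Then do one of the following:
   - relabel the both-visits set as complete-case and drop the per-protocol name; or
   - define per-protocol by a criterion on the Section 2.3 adherence ratio plus major deviations in either arm. The trial team should set the threshold.
3. If per-protocol is kept, fix its definition before outcome data are analysed. Unblinding is not a clear cut-off here, because Section 2.2 gives the biostatistician and data manager access to the allocation sequence. Report the result as supportive and say that selecting adherers breaks randomisation.

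The cost is wording only. The adherence data are already collected and the sample size does not change. A redefined per-protocol set will be smaller, with a wider confidence interval.

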## 3. Discussion

Lower-extremity electrical stimulation is an older technique that has regained recent interest in the treatment of lower extremity functional impairment of people with PAD, as shown by recently published original and protocol studies [49,50,51,52]. Owing to the very low number of available studies with adequate sample size and low risk of bias, a recent systematic review concluded that no clear clinical indication could be drawn regarding the efficacy of NMES for the management of impaired walking function in patients with PAD [13]. The multicenter, investigator-blinded, randomized controlled ELECTRO-PAD clinical trial will contribute to increase the level of scientifical evidence regarding the efficacy on NMES on walking capacity in people with lower extremity PAD.

One strength of the ELECTRO-PAD clinical trial is the duration of the NMES program. As compared to previous studies that assessed the effect of an NMES program on walking capacity during four-week or a six-week programs [12,14,49], the NMES program of the ELECTRO-PAD trial is longer, with a three-month program duration which duplicates the recommended duration for SET programs [8]. It will be of interest to observe the magnitude of change (if any) in walking capacity from the ELECTRO-PAD trial compared to previous NMES programs and SET programs.

Another strength of the ELECTRO-PAD clinical trial relies on the methods used for the assessment of walking capacity. Compared with previous studies [12,14,49], the ELECTRO-PAD clinical trial will assess the walking capacity of PAD participants through three complementary walking assessment tests: the modified Strandness treadmill test, the six-minute walking test, and a GPS-assessment of outdoor walking capacity. Although this increases the complexity of the protocol, this methodologic choice was deemed important considering the existing controversy about the best functional test for measuring response to interventions in PAD [31,53,54]. It has been shown that walking capacity assessment tests provide outcomes that are not interchangeable in participants with PAD [55]. The ELECTRO-PAD clinical trial will show whether, and how, an NMES program impacts differently walking capacity changes according to the outcome measure that is considered.

Potential study limitations should also be considered. First, in the design of the ELECTRO-PAD clinical trial, careful consideration was given to the definition of the control group since the lack of an appropriate control group was clearly a major bias in previous studies [13]. For instance, the two only available randomized controlled trials testing home-based NMES programs alone to improve walking performance used transcutaneous electrical nerve stimulation as a placebo [12,14], whereas this type of lower-extremity electrical stimulation was reported to increase walking capacity in PAD participants in another study [56]. In the ELECTRO-PAD study, the choice was made to use a control group with participants receiving lifestyle advice, including walking advice, together with best medical therapy, as this was considered to be the best solution both at the methodological (intention to treat approach) and ethical levels [13]. Indeed, although the use of a sham intervention could be seen as an ideal way to design double-blind studies, it raises issues with regards to the ethics of volunteer deception and the risk of volunteer awareness of the sham treatment, with a subsequent risk of unbalanced dropout rates between groups. In addition, following a 12-week program would exacerbate the sedentary behavior and worsen the functional impairment of a sham control group [57].

Second, supervised exercise therapy (SEP) is recommended as the first-line therapy to decrease leg symptoms and improve walking capacity in people with PAD [3,8]; thus, administering SEP to the control group could have been considered as an attractive option. When designing the ELECTRO-PAD clinical trial, the choice was made not to use a SEP-intervention control group since the availability of SEP programs in France is extremely low. Even when available, SEP programs are shorter in duration (~3–4 weeks) compared to current practice guidelines [8]. Undoubtedly, this would have been seen as a major limitation when comparing walking capacity changes between the control (SEP) group and the NMES group. Interestingly, Babber et al. recently showed a significant adjunctive benefit of a footplate NMES program in PFWD improvement, but not in MWD improvement, when NMES was used as an adjunct to SEP compared to SEP alone [49].

Finally, the participants with bilateral lesions apply NMES on one calf during half of the program session, then on the other calf for the other half-session. Thus, the duration of the NMES session for each limb for participants with bilateral lesions is two times less than the session duration for participants with a unilateral lesion. The device used does not allow the user to simultaneously connect two pairs of electrodes (i.e., one for each limb). Another possible solution could have been to use two devices simultaneously in participants with bilateral lesions. However, we did not choose this solution because we expected this could have been too burdensome for those participants, increasing the risk of low adherence to the NMES program or dropout. The inclusion of participants with bilateral lesions is deemed important for a wider applicability of NMES intervention in people with PAD in the future. We foresee that there will be few participants with walking limitations due to strictly equal bilateral symptoms at the calf level. Nevertheless, we will assess whether the change in maximal walking distance differs according to the participant’s symptom profile (i.e., bilateral vs unilateral).

## Figures and Tables

**Figure 1 jcm-11-07261-f001:**
[figure not shown]
Flowchart for participant screening for eligibility, inclusion, assessments, randomization, interventions, and follow-up. ***Legend.*** WIQ: Walking Impairment Questionnaire; PAQ: Peripheral Artery Questionnaire; FFQ: Food Frequency Questionnaire; TcPO_2_: Transcutaneous oxygen pressure measurement; PA: Physical Activity; GPS: Global Positioning System; NMES: Neuromuscular Electrical Stimulation. Note that participants’ allocation to NNMS or CONTROL groups following randomization is concealed to the participants until they complete the 7-day physical activity measurement.

**Figure 2 jcm-11-07261-f002:**
[figure not shown]
Photo showing the VEINOPLUS^®^ device at the calf level.

**Table 1 jcm-11-07261-t001:** Inclusion and exclusion criteria of the ELECTRO-PAD clinical trial.

**Inclusion Criteria**
Age > 40 years old. Subjects with Lower Extremity Peripheral Artery disease (LEPAD). LEPAD is defined by the presence of at least one of the following criteria: History of revascularization in the lower limbs due to LEPAD OR Ankle brachial index (ABI) of ≤0.90 ^1^ OR ABI or ankle systolic blood pressure decrease during recovery from treadmill walking test >20% or >30 mmHg, respectively OR Toe-brachial index ≤ 0.70 if ABI cannot be measured and if incompressible arteries are suspected Complain of exertional calf pain (fatigue, discomfort or cramping) that can begin or not at rest, causes the participant to stop walking and relieves or lessens within 10 min of rest (assessed using the San Diego questionnaire AND confirmed during treadmill testing). Pain (fatigue, discomfort, or cramping) that is mainly located at the calf level. Maximal walking distance on treadmill < 300 m (treadmill protocol: 3.2 km/h, 10% grade). Subject receiving for at least one month the recommended medical therapy for LEPAD management (antiplatelet therapy and statin medication). Obtained informed consent.
**Exclusion Criteria**
Patients with a pacemaker or defibrillator. Patients with acute or critical limb ischemia. Ambulation limited by exertional symptoms other than intermittent claudication (e.g., dyspnea or angina pectoris). Ambulation limited by exertional symptoms indicative of intermittent claudication but affecting muscles in the lower extremities other than the calves. Contraindication to exercise testing according to the American Heart Association and the American College of Sports Medicine. Major cardiovascular event (myocardial infarction or stroke) or major surgery within the previous three months before inclusion. Female patients who are pregnant, planning to become pregnant, or lactating. Known presence of an aneurysm of the abdominal aorta > 4 cm or an aneurysm of the iliac artery > 1.5 cm. Patient subject to legal protection (guardianship or tutelage measure) and persons deprived of their liberty (according to French law). Simultaneous participation in another ongoing clinical research protocol. Unwilling or unable to engage in the completion of a 12-week program. Any planned event(s) that could interfere with the completion of the protocol: e.g., extended holidays preventing the completion of the intervention or planned hospitalization for a prolonged period. Body mass > 160 kg (may exceed treadmill limit). Inability to understand and sign informed consent forms due to cognitive or language barriers. LEPAD due to causes other than atherosclerosis.

^1^ PAD is defined by an ankle–brachial index (ABI; the ratio of the systolic blood pressure at the ankle to the systolic blood pressure in the arm) of 0.90 or less. An ABI is considered as “borderline” between 0.91 and 0.99, “normal” between 1.00 and 1.40, or “noncompressible” when >1.40 [3].

## Data Availability

Not applicable.
